### Staff recruitment and training

Prevention, education, treatment, Training and Research-Global Solutions (PeTR-GS), our local PEPFAR-supported partner working with the Sunrise Foundation, conducted training workshops for all study staff and church-based lay health advisors. They received training on the study protocol, including how to obtain informed consent, data collection forms, and confidentiality. Additionally, study staff received information on HIV counseling, delivering HIV test results and post-test counseling. Although priests are not involved in the active intervention, they also received information focused on basic HIV transmission, MTCT and PMTCT that will be useful should any participant identified as HIV-infected request counsel from the priest. Attempts were made to preferentially recruit individuals who have previously completed HIV training programs through PeTR-GS or other agencies to reduce the time spent in training. The training was a modified format used by PeTR-GS for national HIV counseling and testing training.

### Participant recruitment

Recruitment began following randomization of the churches. Each Sunday, the priest asks pregnant women and their male partners in the congregation to step to the altar for prayers. He prays for a healthy pregnancy, successful delivery, and encourages pregnant women to seek care at a health facility during their pregnancy. He introduces the concept of the Healthy Beginning Initiative and study team as a program supporting pregnant women in the congregation during pregnancy. Pregnant women and their male partners are encouraged to participate. Pregnant women who consent can participate in the study, even when the male partner is unavailable or chooses not to participate.

### Description of the intervention

Intervention is focused on removing system-level barriers to HIV testing and making tests available to pregnant women where they congregate as close to their home environment as possible. Conducted as part of a church-organized, family-oriented baby shower program that celebrates pregnancy and childbirth, the integrated approach to laboratory tests could potentially reduce the stigma associated with an HIV-only test approach (Figure 
2).

**Figure 2 F2:**
[figure not shown]
Summary of intervention activities.

### Description of the control condition/usual care

Participants in churches randomized to CG also follow the three steps of priest-directed prayer sessions, baby shower, and a church-organized baby reception. An edutainment game and free integrated on-site laboratory tests are not offered during the baby shower for this group. Pregnant women were encouraged to attend prenatal care through the health facilities. Participants also complete a post-delivery questionnaire. The research team maintains direct contact with health facilities to confirm HIV testing and PMTCT completion.

### Outcome measures

The primary outcome measure is HIV testing for pregnant women and pertains to both the cluster and individual participant level. Post-delivery questionnaires will be used to ascertain HIV testing during pregnancy. HIV testing during pregnancy will be confirmed through the integrated laboratory testing at churches randomized to IG. HIV testing among women in churches randomized to CG will be confirmed at the health facility where pregnant women reported prenatal care. The secondary outcomes are male partner HIV testing and PMTCT completion among HIV-infected women, and pertain to both the cluster and individual participant level.

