**Methods:**

This cluster randomized trial tests the comparative effectiveness of a congregation-based Healthy Beginning Initiative (HBI) versus a clinic-based approach on the rates of HIV testing and PMTCT completion among a cohort of church attending pregnant women. Recruitment occurs at the level of the churches and participants (in that order), while randomization occurs only at the church level. The trial is unblinded, and the churches are informed of their randomization group. Eligible participants, pregnant women attending study churches, are recruited during prayer sessions. HBI is delivered by trained community health nurses and church-based health advisors and provides free, integrated on-site laboratory tests (HIV plus hemoglobin, malaria, hepatitis B, sickle cell gene, syphilis) during a church-organized ‘baby shower.’ The baby shower includes refreshments, gifts exchange, and an educational game show testing participants’ knowledge of healthy pregnancy habits in addition to HIV acquisition modes, and effective PMTCT interventions. Baby receptions provide a contact point for follow-up after delivery. This approach was designed to reduce barriers to screening including knowledge, access, cost and stigma. The primary aim is to evaluate the effect of HBI on the HIV testing rate among pregnant women. The secondary aims are to evaluate the effect of HBI on the rate of HIV testing among male partners of pregnant women and the rate of PMTCT completion among HIV-infected pregnant women.

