## Methods

### Study design

Using a two-arm cluster randomized trial design, we will evaluate the effect of a congregation-based HBI that provides free, integrated on-site laboratory tests during a church-organized baby shower as the IG versus clinic-based approach as the CG on the rate of HIV testing among pregnant women, their male partners, and the PMTCT completion rate among HIV-infected pregnant women. A total of 40 churches in Enugu State, south-east Nigeria, will be randomly assigned to either the IG (N = 20 churches) or the CG (N = 20 churches). A total of 2,700 pregnant women will be enrolled in this study, with about 8 to 16 pregnant women each month per church (depending on the size of the church) enrolled each month over a 5-month period. Participants in churches randomized to the CG will be referred to the closest healthcare facility for HIV testing and prenatal care. Participants in churches randomized to IG will receive health education and be offered an HIV test as part of an integrated laboratory test on-site at the church during a baby shower program. The primary outcome is difference in the rate of HIV testing between both groups. The secondary outcomes are the difference in the rate of HIV testing among male partners, and the PMTCT completion rate among HIV-infected pregnant women in both groups. Pregnant women will complete an investigator-administered questionnaire to collect information on HIV testing and PMTCT completion. Self-reported HIV testing and PMTCT completion will be confirmed with the healthcare facility for participants in churches randomized to the CG, and with on-site HIV testing data and the healthcare facility (PMTCT completion) for participants in churches randomized to the IG (Figure 
1). Participants in churches randomized to CG will have two study visits: baseline (recruitment) and six to eight weeks after delivery. Participants in churches randomized to IG will have three study visits; baseline (recruitment), baby shower and six to eight weeks after delivery.

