### Study setting and participants

We selected Enugu State as the site for the proposed study for three reasons: first, its population is culturally and ethnically related and predominately Christian, with church attendance approaching 90%
[43,44]. Second, the overall state HIV sero-prevalence of 5.1% is close to the national average of 4.1%
[8]. Third, the churches that we propose to use as study sites are widely distributed in Enugu and Oji-River areas, and represent variations in the prevalence rate across the state of 4% to 8% (6% average)
[8]. Any self-identified pregnant woman attending any of the study sites is eligible to participate. Women are encouraged to participate with their male partners, but can still participate if the male partner chooses not to participate. The study was approved by the Institutional Review Board of the University of Nevada, Reno, and the Nigerian National Health Research Ethics Committee.

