### Statistical methods

All three hypotheses test for differences in two binomial proportions at follow-up. Clustering effects must be incorporated in the analysis since data collected on parishioners within the same church could be expected to exhibit correlation, while data collected on parishioners in different churches should exhibit minimal correlation. Generalized linear mixed models as implemented in PROC GLIMMIX in SAS 9.3
[47] provide a rich set of tools for analyzing such data. Data will be analyzed with that procedure using a logit link function and the binomial distribution. These are multilevel models allowing incorporation of covariates and confounders for the individual (such as age, household income, education level, previous HIV testing, last menstrual period, marital status, employment status, male’s partners’ previous HIV test results, and situational/contextual factors) and cluster-level (*i.e.*, church) covariates and confounders such as size of church and congregation type (Anglican or Catholic). For all three hypotheses, a preliminary (and similar) analysis will model the probability that an individual declines participation; any significant predictors from that model will be used in the main analysis to reduce confounding. Statistical significance will be set as p-value <0.05 and tests will be 2-sided.

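### HIV testing is ascertained after delivery, but only the intervention arm has an earlier test record, so women lost before that contact are ascertained differently by arm

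*Protocol article*

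**What the plan says.** All references are to the protocol article.

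- **Who enters.** Study setting and participants: "Any self-identified pregnant woman attending any of the study sites is eligible to participate". Sample size and power analysis adds that women join at varying stages of pregnancy.
- **When they are seen.** Study design: "Participants in churches randomized to CG will have two study visits: baseline (recruitment) and six to eight weeks after delivery", and "Participants in churches randomized to IG will have three study visits; baseline (recruitment), baby shower and six to eight weeks after delivery". Description of the control condition gives the CG a shower too, but without on-site tests, and Study design does not count it as a CG study visit.
- **How the primary outcome is obtained.** Outcome measures: "Post-delivery questionnaires will be used to ascertain HIV testing during pregnancy". For the IG, "HIV testing during pregnancy will be confirmed through the integrated laboratory testing at churches randomized to IG". For the CG, "HIV testing among women in churches randomized to CG will be confirmed at the health facility where pregnant women reported prenatal care".
- **Where follow-up happens.** Abstract, Methods: "Baby receptions provide a contact point for follow-up after delivery".
- **Who is analysed.** The end of Sample size and power analysis describes an intention-to-treat analysis of randomised participants who had their initial test, including those who drop out afterwards.
- **What is already collected.** Statistical methods lists "last menstrual period" among the individual covariates.

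**The concern.** The outcome is whether a woman was tested during pregnancy, and both arms are asked about it after delivery. The two arms do not depend equally on that contact. An IG woman tested at the shower has a study record whether or not she is seen again. A CG woman's test is found through what she reports and a check at the facility she reports, and no CG study visit falls between baseline and the post-delivery one. The condition on initial testing in the analysis set points the same way: it retains IG women with an on-site test and has no CG counterpart, since the study offers CG women no test.

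A woman lost between the shower and the last contact can thus count as tested in the IG, while the same woman in the CG may be recorded as untested or dropped. Either treatment can move the comparison towards the intervention. Early pregnancy loss shows this most plainly: with no delivery, the visit rule sets no date on which she should be contacted.

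**Working it through.** **Sources side by side, for a woman lost before the post-delivery contact**

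| | IG | CG |
|---|---|---|
| Study visit between baseline and post-delivery | Baby shower | None |
| Study test record made before delivery | Yes, if tested at the shower | None, no test offered |
| Facility check for HIV testing | Not needed for an on-site test | At the facility she reports |
| Analysis-set condition (initial test done) | Met by the on-site test | No study test that could meet it |
| Visit date if pregnancy ends early | Not defined | Not defined |

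The last row is the same in both arms. The difference by arm comes from the rows above it.

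**The plan's own attrition figure.** The article allows 10% dropout, taken from community HIV testing: (140/0.06)/0.9 = 2,593, stated as approximately 2,700. This inflates the number enrolled. It neither describes loss during pregnancy follow-up nor corrects a bias that runs in one direction.

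**Illustration of size.** Inputs from Sample size and power analysis: CG rate p = 0.15 to 0.25, 1,350 women per arm, 40 churches (2,700/40 = 67.5 women each), ICC 0.002 to 0.10. Assumed, because the documents give no figure: a proportion L = 2% to 15% lost before the contact, equal true testing rates in the two arms, and every tested IG woman tested on site before loss.

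*Case A: unreached CG women count as untested, IG log stands.* Recorded CG rate = p(1 − L); artefact = pL.

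- p = 0.20: L = 2% gives 0.196 (0.4 points); 5% gives 0.190 (1.0); 10% gives 0.180 (2.0); 15% gives 0.170 (3.0).
- Over p = 0.15 to 0.25: from 0.15 × 0.02 = 0.3 points to 0.25 × 0.15 = 3.8 points.

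*Case B: unreached women leave the denominator unless an on-site record exists.* Recorded IG rate = p/[p + (1 − p)(1 − L)], and the CG stays at p. At p = 0.20 and L = 2%: 0.20/0.984 = 0.203 (0.3 points). At L = 15%: 0.20/0.88 = 0.227 (2.7 points).

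*Case C: unreached women are excluded in both arms whatever records exist.* No arm difference arises from this source, provided loss and testing are unrelated.

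**Set against the trial's precision.** Effective n per arm = 1,350/(1 + 66.5 × ICC), which is 1,192, 312 and 176 at ICC 0.002, 0.05 and 0.10. At p = 0.20 and 80% power, the minimum detectable differences are 4.8, 9.7 and 13.2 points. The same method applied to the rates in Table 2 gives power of 0.77–0.82 in 44 of 45 cells, and 0.72 in one where two-decimal rounding explains it, so it matches the article's calculation. The Case A artefact at p = 0.20 is below all three differences.

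It still shifts the false-positive rate. With no true effect, the chance of a significant result favouring the IG is Φ(d/SE − 1.96), where d = pL and SE = √{[p(1 − p) + p(1 − L)(1 − p(1 − L))]/n}. For p = 0.20, L = 15%, ICC 0.05: SE = √(0.3011/312) = 0.0311, d/SE = 0.97, probability 0.16. Over L = 2% to 15% the range is 0.043–0.47 at ICC 0.002, 0.033–0.16 at 0.05 and 0.031–0.11 at 0.10, against a nominal 0.025.

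**The case against.** The best defence is that the CG is not left without routes to the outcome. Study design refers CG women to the closest healthcare facility, so a place to look can be identified without the questionnaire. Description of the control condition has the team in direct contact with facilities. Outcome measures does not say when a woman reports her facility. Trial status commits to following each participant through pregnancy and up to eight weeks post-delivery. The IG advantage is also incomplete: a woman who miscarries before the shower has no on-site record either, and the timing of the shower is not given. All of this stands, and it makes the figures above upper-end. It does not remove the asymmetry, because the stated CG check runs through the facility the woman reports, and the analysis-set condition has no CG equivalent.

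A reader might infer more than the documents support:

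- *That any woman who loses a pregnancy or infant has no outcome contact.* The visit is timed from delivery, not from a live birth. Stillbirth is a delivery, and an infant death leaves the visit date unchanged. The reception is one contact point, and the questionnaire is not said to be given only there. Only early loss, or a woman who proves not to be pregnant, lacks a date.
- *That PMTCT completion suffers from the same on-site log.* Study design confirms PMTCT completion at the healthcare facility in both arms.
- *That pregnancy losses go unrecorded, or that safety information is forgone.* This would rest on the silence of a condensed article. Pregnancy loss is not a stated outcome, and the full protocol and forms are not shown.

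**Conclusion.** The point holds in a limited form. Women lost before the post-delivery contact, for any reason, are better ascertained for HIV testing in the IG than in the CG, and the resulting bias favours the intervention. Early pregnancy loss is the clearest instance, not the whole of it.

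The size cannot be fixed from the documents. The 0.4–3.0 points at a 20% CG rate require three assumptions together: 2–15% of CG women unreached, no facility record retrieved for any of them, and all counted as untested, while the IG record is complete. Relaxing any of these shrinks the artefact. Against the large increase the trial hopes for, it would not create the main finding, but it could exaggerate a modest effect or raise the false-positive rate. It is worth correcting because it runs one way and most of it is avoidable.

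**What to change.** 1. Date the final visit six to eight weeks after the end of pregnancy, however it ends. Set a latest due date for each woman from the last menstrual period already collected, so that a contact falls due even when no delivery is reported.
2. Obtain the prenatal facility before the final visit in both arms: at baseline for women still to be enrolled, and at the next contact or from the referral facility for those already in. Trial status reports 2,000 of an expected 5,400 participants recruited, so a new baseline item alone would not cover everyone.
3. Check facility records for every CG woman, whether or not she is reached.
4. Replace the initial-testing condition with all enrolled women in both arms, and classify unreached women by the same rule in both arms.
5. Add a sensitivity analysis for missing outcomes, including one that sets aside the on-site record of unreached IG women so that both arms are treated as in Case C.

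The cost is a revised visit window, one facility item on existing forms and a rewritten analysis-set sentence, plus some contacts outside the baby reception and additional record checks at facilities the team already deals with.

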2, it appears safe to target between cluster sizes 3 and 4, for a total sample size of 140 HIV-infected women. Using the average of 6% of pregnant women infected with HIV, and a possible 10% dropout rate (from our experience during scale up of community HIV testing), that would require (140/0.06)/0.9 or approximately 2,700 total pregnant women (1,350 per group). Clearly, any interesting increase in rate for the intervention group is detectable for such a large total sample size for Hypotheses 1 and 2 (Table 
2).

**Table 2 T2:** Minimum detectable intervention group rate (2-sided test, 5% significance level)

**Cluster size (total sample size)**	**Control group rate**								
	**0.15**			**0.20**			**0.25**		
	**ICC**			**ICC**			**ICC**		
	0.002	0.05	0.1	0.002	0.05	0.1	0.002	0.05	0.1
3 (120)	0.37	0.38	0.39	0.43	0.44	0.45	0.49	0.50	0.51
4 (160)	0.34	0.35	0.36	0.40	0.41	0.43	0.46	0.47	0.49
5 (200)	0.31	0.33	0.35	0.38	0.39	0.41	0.43	0.45	0.47
10 (400)	0.26	0.29	0.31	0.32	0.35	0.37	0.38	0.41	0.43
50 (2000)	0.20	0.24	0.27	0.25	0.30	0.33	0.31	0.36	0.39

Number of churches needed (K): We need to have 1,350 pregnant women in each arm of the study and follow them through pregnancy and up to six weeks post-delivery. Since pregnant women will be recruited at different stages of pregnancy, we will need to end recruitment five months after the study is open to recruitment and allow time to follow the last recruited pregnant women through nine months of pregnancy and up to six to eight weeks post-delivery (approximately eleven months). According to our review of infant baptisms in churches in our proposed study area, there were more than 50 churches with 200 infant baptisms per year (an average of 16 per month) and 20 churches with more than 100 infant baptisms per year (an average of 8 per month). We will need to recruit 15 of the large churches and 5 of the small churches in each arm to reach our sample size of 1,350 pregnant women in each arm over a 5-month period. Table 

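### HIV testing is confirmed from different sources in the two arms: a facility test can be confirmed in the control arm but has no stated route in the intervention arm

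*Protocol article*

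**What the plan says.** Under Outcome measures, the article sets one instrument and one nominal window for everyone: "Post-delivery questionnaires will be used to ascertain HIV testing during pregnancy". It then names a different check for each arm. For IG: "HIV testing during pregnancy will be confirmed through the integrated laboratory testing at churches randomized to IG". For CG: "HIV testing among women in churches randomized to CG will be confirmed at the health facility where pregnant women reported prenatal care".

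Study design gives the same split. For CG: "Self-reported HIV testing and PMTCT completion will be confirmed with the healthcare facility for participants in churches randomized to the CG". For IG: "with on-site HIV testing data and the healthcare facility (PMTCT completion) for participants in churches randomized to the IG". The bracketed label ties facility contact in IG to PMTCT completion, not to HIV testing.

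Three further statements matter:
- The on-site test belongs to the baby shower, which Study design lists after recruitment: "Participants in churches randomized to IG will have three study visits; baseline (recruitment), baby shower and six to eight weeks after delivery".
- Entry is open at any gestation (Sample size and power analysis): "Since pregnant women will be recruited at different stages of pregnancy".
- A test earlier in the same pregnancy does not exclude a woman (Study setting and participants): "Any self-identified pregnant woman attending any of the study sites is eligible to participate".

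Statistical methods names earlier HIV testing and last menstrual period only as possible covariates.

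**The concern.** A facility test can be verified in CG whenever in the pregnancy it took place. In IG the only stated check is the church test, so a facility test has no verification route, whether it came before or after enrolment. Take two women with the same history: tested at a clinic in this pregnancy, not tested at church. If verification decides the outcome, the CG woman counts as tested and the IG woman does not.

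Randomization balances how often such tests occur, but not whether they count. Covariate adjustment does not repair it either, because the outcome itself is ascertained differently by arm. At stake are the size and meaning of the primary difference, which this component pushes against HBI.

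**Working it through.** **Benchmark from the plan.** The design implies 2,700/40 = 67.5 women per church, so the nearest row of Table 2 is cluster size 50. At a CG rate of 0.20 it gives detectable IG rates of 0.30 (ICC 0.05) and 0.33 (ICC 0.10), which are differences of 10 and 13 points. An unpooled two-proportion test with 20 churches per arm, design effect 1 + (50-1)*ICC and two-sided 0.05 gives 0.301 and 0.334. This assumes 80% power, which the table does not state. The benchmark therefore reproduces.

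**Inputs**
- CG rate of any test in pregnancy: 0.20, within the planned 15-25% (Sample size and power analysis).
- q, share tested at a facility before enrolment: not given; assumed 5-15%.
- v, share of those women retested on site: not given; shown for several values. The Background reports testing above 80% when women are informed and tests are available, so 0.8 is a reasonable middle case.
- u, on-site uptake in the other women: not given.

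**Step 1: tests before enrolment.** All of q can be confirmed in CG, but only q*v in IG. The loss in the IG-CG difference is q*(1-v):

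| v | q = 5% | q = 15% |
|---|---|---|
| 0.9 | 0.5 points | 1.5 points |
| 0.8 | 1 point | 3 points |
| 0.5 | 2.5 points | 7.5 points |
| 0 | 5 points | 15 points |

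**Step 2: facility tests after enrolment.** Assume that facility testing is equal in the two arms and independent of on-site uptake. Among women not tested before enrolment, the later facility rate is c = (0.20 - q)/(1 - q). The further loss is (1-q)*(1-u)*c = (0.20 - q)*(1-u).

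**Step 3: example with q = 10%, u = v = 0.5.** Here c = 0.10/0.90 = 0.111.
- IG, on-site test only: 0.9*0.5 + 0.1*0.5 = 0.50. Difference from CG: 30 points.
- IG, any source: 0.1 + 0.9*(1 - 0.5*0.889) = 0.60. Difference from CG: 40 points.
- Loss: 10 points, of which 0.10*0.5 = 5 come from tests before enrolment and (0.20 - 0.10)*0.5 = 5 from tests after it.

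When u = v, the total loss is 0.20*(1-u) whatever q is: 4 points at 0.8, 10 at 0.5 and 14 at 0.3. At 0.3, a 24-point difference would appear as 10.

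**The case against.** The strongest reply is that the article has one window and one questionnaire for both arms, and that the arm-specific sources only confirm the report. It nowhere says that an unconfirmed report is scored as untested. This stands, and it makes the bias conditional: if unconfirmed self-report counts, the gap shrinks. It does not remove the point, because the unequal sources are stated twice and are not a detail left open.

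A reader might infer that the arms have different outcome windows. The documents do not support that. The nominal window is the same, and the asymmetry lies in the source. It also affects facility tests after enrolment, as Step 3 shows.

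A reader might also add a share f of earlier tests to a later CG rate of 0.20 and find CG inflated by f*(1-0.20), or 4-16 points for f of 5-20%. That ignores IG women who retest on site. It also treats the planned CG rate as a post-enrolment rate, which the article does not say. The resulting CG totals are 24-36%, and any f above 0.05/0.80 = 6.25% takes CG beyond the planned 25%. The Background's remark that most women do not access prenatal care early also points to a small share tested before enrolment.

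Finally, one could argue that earlier tests should not count at all, since HBI cannot have caused them. Testing at any time in pregnancy is a legitimate target and matches the population indicator that motivates the trial. Counting only later tests would score a CG woman properly tested at an earlier visit as untested, while a repeat test at church counts as a success. In the Step 3 example it gives 55% - 10% = 45 points, against 40 for any source. That is a change of estimand, not a correction.

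**Conclusion.** The point holds as differential confirmation by arm. If confirmation decides the outcome, the IG-CG difference is understated by q*(1-v) for tests before enrolment: about 1-3 points at v = 0.8 and 2.5-7.5 at v = 0.5, for assumed q of 5-15%. Facility tests after enrolment add a further loss. In the illustration the total is 4 points at 80% on-site uptake and 10 at 50%, against a detectable difference of 10-13 points. These totals rest on a CG rate of 20%, equal facility testing in the two arms, and independence from on-site uptake.

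High uptake, or counting unconfirmed self-report, would make the loss small. Because this component works against HBI, it threatens the size of the estimate more than it risks a false-positive result. It should be corrected, but it does not undermine the trial.

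**What to change.** Under Outcome measures, and to match under Study design:
- Accept on-site test data and facility records as confirmation of HIV testing in both arms.
- State one rule, the same in both arms, for scoring a report that neither source confirms.
- Record the date of each test on the questionnaire and the facility form.
- Keep testing at any time in pregnancy as the primary window.
- Add a sensitivity analysis limited to tests dated after enrolment, or to women not tested earlier in this pregnancy.

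The cost is small. The team already contacts facilities for CG women, and for PMTCT completion in IG, so the additions are one more item in the IG facility check and a test date. Some facility records may lack a date, which would limit the sensitivity analysis but not the primary one.

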### Church recruitment and randomization

Recruitment occurred at the level of the churches and participants (in that order), while randomization occurred only at the church level. A total of 40 churches selected from four dioceses (the Anglican diocese of Enugu, the Catholic diocese of Enugu, the Anglican diocese of Oji-River, and the Catholic diocese of Agwu) were randomized to either the IG or the CG. All of the bishops who oversee churches in the proposed study areas had previously agreed to participate in this study and gave the study team access to speak to the priests under their dioceses. Randomization of churches occurred in 4 cohorts of 10 churches following random ranking. The churches were randomized in a 1:1 ratio to either the IG or CG. The sequence of randomization was generated by [name] and kept in a sealed opaque envelop away from the study sites in accordance with CONSORT guidelines
[45]. Once the sites had been recruited and baseline information on churches collected (*e.g.*, type, size of congregation), the sites were informed of their randomization group and assigned a code. Because of the nature of the intervention, it was impossible to blind the participants, community health nurses, lay health advisors, and study coordinators to the group assignment, but the test results cannot be influenced by the study coordinators.

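### HIV testing, the primary outcome, is confirmed from different sources in the two arms; if confirmation decides the outcome, this risks inflating the effect

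*Protocol article*

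**What the plan says.** The Outcome measures section starts from one instrument for everyone: "Post-delivery questionnaires will be used to ascertain HIV testing during pregnancy". It then names a separate confirmation source for each arm:

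- IG: "HIV testing during pregnancy will be confirmed through the integrated laboratory testing at churches randomized to IG".
- CG: "HIV testing among women in churches randomized to CG will be confirmed at the health facility where pregnant women reported prenatal care".

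The Study design section repeats the split. For the CG, "Self-reported HIV testing and PMTCT completion will be confirmed with the healthcare facility for participants in churches randomized to the CG". For the IG, confirmation is "with on-site HIV testing data and the healthcare facility (PMTCT completion) for participants in churches randomized to the IG", so the facility is consulted about PMTCT completion and not about testing.

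The section on the control condition describes the effort behind CG confirmation: "The research team maintains direct contact with health facilities to confirm HIV testing and PMTCT completion". The Study design section also gives the arms different contact: "Participants in churches randomized to CG will have two study visits: baseline (recruitment) and six to eight weeks after delivery", whereas the IG has an additional baby shower visit at which testing is offered. On blinding, the section on church recruitment and randomization accepts that staff and participants know the allocation, "but the test results cannot be influenced by the study coordinators".

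**The concern.** The primary comparison is the proportion of women tested, so each arm's count must come from an equally sensitive process. As written, it does not.

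An on-site IG test is carried out and recorded by the trial during pregnancy. A CG test is confirmed only if the woman reports it after delivery and the facility she named for prenatal care has a record of it. A test at another facility, or one that was poorly recorded, has no stated route to confirmation.

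The remark that coordinators cannot influence test results does not settle this. The outcome is whether a test took place, not what it showed, and unblinded staff collect that information.

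At stake is a difference between arms that comes from the measurement. It would probably favour the intervention, and a larger sample would not remove it.

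**Working it through.** **1. Sources side by side (Outcome measures; Study design)**

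| Where the test took place | IG | CG |
|---|---|---|
| On site at the church | Confirmed from trial data | Not offered |
| Facility named for prenatal care | No confirmation of testing stated | Confirmed at that facility |
| Any other place | No confirmation stated | No confirmation stated |

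Self-report by questionnaire applies to all cells. The asymmetry lies only in the confirmation step.

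**2. The plan's own yardstick (Table 2)**

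Inputs: 20 churches per arm, 50 women per church, ICC 0.05, CG rate 0.20, two-sided 5% test. The article states no power; 80% is inferred because it reproduces the table.

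- Design effect = 1 + (50 − 1) × 0.05 = 3.45.
- Effective n per arm = 20 × 50 / 3.45 = 289.9.
- With an IG rate of 0.30, SE = √[(0.20 × 0.80 + 0.30 × 0.70) / 289.9] = 0.0357.
- Detectable difference = (1.96 + 0.84) × 0.0357 = 0.10.

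This gives 0.30, as in Table 2. The same formula matches all 45 cells to within 0.006.

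**3. Spurious difference if confirmation decides the outcome**

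Let p be the true testing rate in both arms (no effect) and s the share of CG tests that tracing captures. Assume full IG capture and score unconfirmed CG tests as untested. The document gives no value for s; 0.80 to 0.95 is assumed.

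Spurious difference = p − s × p = p(1 − s).

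- p = 0.20, s = 0.95: 0.20 × 0.05 = 1 point.
- p = 0.20, s = 0.90: 0.20 × 0.10 = 2 points.
- p = 0.20, s = 0.80: 0.20 × 0.20 = 4 points.

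Over the plan's anticipated CG range of 15% to 25%, the result runs from 0.15 × 0.05 = 0.75 points to 0.25 × 0.20 = 5 points. Table 2's differences at 50 per church and ICC 0.05 are 9, 10 and 11 points for CG rates of 15%, 20% and 25%.

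**4. Effect on type I error at the planned size**

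Inputs: 1,350 women per arm in 20 churches (67.5 per church). Effective n per arm = 1,350 / (1 + 66.5 × ICC), which is 312.1 at ICC 0.05.

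P(reject) = Φ[(d − 1.96 × SE0)/SE1] + Φ[(−d − 1.96 × SE0)/SE1], where d is the spurious difference, SE0 the pooled and SE1 the unpooled standard error.

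Example, s = 0.90 and ICC 0.05: d = 0.02 and SE0 ≈ SE1 ≈ 0.0314. This gives Φ(−1.32) + Φ(−2.60) ≈ 0.093 + 0.005 = 0.098.

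| CG capture s | Difference | ICC 0.002 | ICC 0.05 | ICC 0.10 |
|---|---|---|---|---|
| 0.95 | 1 point | 9% | 6% | 6% |
| 0.90 | 2 points | 24% | 10% | 8% |
| 0.80 | 4 points | 72% | 26% | 16% |
| Equal in both arms | 0 points | 5% | 5% | 5% |

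For scale, the detectable difference at 67.5 per church and a CG rate of 0.20 is about 5, 10 and 13 points at the three ICCs.

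**5. The offset from the IG**

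If a share q of IG tests takes place only at a facility and also goes unconfirmed, the spurious difference becomes p[(1 − q) − s]. With p = 0.20, s = 0.90 and q = 0.05 (assumed), it is 0.20 × 0.05 = 1 point instead of 2. The document gives no value for q.

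**The case against.** The strongest reply is that the questionnaire governs. It is given to both arms, and confirmation is described as a check on it. Nothing in the article says that an unconfirmed self-report, or a woman lost before the post-delivery visit, counts as untested. If self-report stands, failed tracing removes nothing from the CG. How discordant sources are resolved is also something an article may leave to the full protocol or the analysis plan, so its absence is no fault here. The team does keep direct contact with facilities.

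Most of this stands, and it rules out some readings that a reader might infer:

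- *That CG under-counting is built in.* This needs a scoring rule that the article does not contain.
- *That the on-site record is complete.* The article does not say so. Its Discussion reports that forms and blood collection kits ran out early on.
- *That the 10% dropout further lowers the CG rate.* That figure is a sample-size allowance. Nothing scores lost women as untested, and loss before the questionnaire can occur in either arm.
- *That the artefact could match the effect the trial is designed to detect.* At ICC 0.05 and within the anticipated 15% to 25% CG range, step 3 stays well below Table 2. Larger losses need a higher control rate or poorer tracing than is assumed here. Only at ICC 0.002 does a 4-point artefact come close to the detectable 5 points.

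What the reply does not remove is the stated text. Two sections prescribe a different confirmation source for each arm. That is a choice the article makes, not a detail it omits.

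**Conclusion.** The point holds as differential verification of the primary outcome in an unblinded trial, with a risk of inflating the effect. The likely direction favours the intervention, because the tests the intervention adds are those the trial itself records. Unconfirmed facility tests among IG women offset part of this.

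The size is illustrative and rests on four assumptions: equal true rates of 20%, full IG capture, unconfirmed CG tests scored as untested, and 80% to 95% CG capture. Under these the spurious difference is 1 to 4 points. Type I error is 6% to 26% at ICC 0.05, and 6% to 72% across the three ICCs in Table 2. If self-report alone defines the outcome, confirmation causes no such loss. Against a true effect of the size the trial can detect, the bias would overstate the estimate rather than create it.

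**What to change.** In the Study design and Outcome measures sections, state one definition and one counting rule for both arms. For example: a woman counts as tested during this pregnancy according to the post-delivery questionnaire, applied identically to all women, with the same rule in both arms for women lost before that visit.

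Add two sensitivity analyses:

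- (a) count only tests confirmed by a record;
- (b) count a test shown by any source.

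For both, seek on-site and facility records in the same way for women of both arms, and query facilities from a single list without arm labels.

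The definition itself costs only wording. The real cost is facility look-ups for IG women. The plan now implies these for HIV-infected women only, about 0.06 × 1,350 = 81; covering all 1,350 would be about 17 times as many (1,350 / 81 = 16.7). The look-ups can instead be limited to women who report a facility test, or to an equal random sample in each arm. No new study visits are needed.
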